## Abstract

**Background:**

It is estimated that about 275,000 inhabitants experience an out-of-hospital cardiac arrest (OHCA) every year in Europe. Survival in out-of-hospital cardiac arrest is relatively low, generally between five per cent and 10%. Being able to explore new methods to improve the relatively low survival rate is vital for people with these conditions. Passive leg raise (PLR) during cardiopulmonary resuscitation (CPR) has been found to improve cardiac preload and blood flow during chest compressions. **The aim of our study** is to evaluate whether early PLR during CPR also has an impact on one-month survival in sudden and unexpected out-of-hospital cardiac arrest (OHCA).

**Method/Design:**

A prospective, randomized, controlled trial in which all patients (≥18 years) receiving out-of hospital CPR are randomized by envelope to be treated with either PLR or in the flat position. The ambulance crew use a special folding stool which allows the legs to be elevated about 20 degrees. Primary end-point: survival to one month. Secondary end-point: survival to hospital admission to one month and to one year with acceptable cerebral performance classification (CPC) 1–2.

**Discussion:**

PLR is a simple and fast maneuver. We believe that the greatest benefit with PLR is when performed early in the process, during the first minutes of CPR and before the first defibrillation. To reach power this study need 3000 patients, we hope that this method article will encourage other sites to contact us and take part in our study.

**Trial registration:**

ClinicalTrials.gov NCT01952197.

## Background

The majority of sudden death cases have a cardiac origin and occur unexpectedly, often outside hospital. Attwood et al. [1] estimated the incidence of and survival from EMS-treated OHCA in Europe and found, for “all-rhythm” CA, an incidence of 37.72 per 100,000 person-years. Survival was 10.7% in “all-rhythm” CA. If these results were applied to the European population, approximately 275,000 persons would experience an all-rhythm, EMS-treated OHCA, with 29,000 persons surviving to hospital discharge [1].

To resuscitate a person, without neurological damage, various efforts, which are described as the four links in the chain of survival (early call, early CPR, early defibrillation and early advanced life support), have to be optimal [2]. During the last decade, the quality and continuity of chest compressions have been increasingly highlighted [3]. The reason is that blood flow and coronary perfusion during cardiac arrest are related to the quality and continuity of chest compressions [4]. A coronary perfusion pressure (CPP) above 15 mmHg, at defibrillation, also appears to be necessary for the return of spontaneous circulation (ROSC) [5]. Consequently, different methods and devices to improve blood flow to the heart (coronary perfusion) and brain during CPR, such as different types of mechanical compressor and impedance threshold device [6-9], have been studied.

The initial CPR guidelines [10-12] stated that the “elevation of the lower extremities may promote venous return and augment artificial circulation during external cardiac compression”. However, in the 1992 guidelines [13], this statement was removed. The reason for this decision was a lack of clinical evidence. During the last five years, the debate on how PLR may improve the outcomes of the resuscitation maneuvers in CPR has been re-opened.

According to Préau et al. [14], the effect of PLR is equivalent to a rapid intravenous volume expander by shifting blood from the lower extremities towards the intra-thoracic compartment. A 45° leg elevation for four minutes increases right and left ventricular preload and, by definition, the stroke volume, if the heart is preload dependent [15]. This makes PLR predictive of fluid responsiveness among patients with circulatory failure, e.g. sepsis and acute pancreatitis [14-17], and it has been recommended as part of haemodynamic monitoring in recent international recommendations [18]. Other researchers have also shown the benefit of using PLR to increase resistance to blood flow [19], thereby shifting fluid from the lower extremities to the central circulation [20,21].

The present study design is based on a pilot study recently conducted in Gothenburg, Sweden. This pilot study concluded that a 20° leg elevation during CPR improved the levels of end-tidal carbon dioxide (EtCO_2_) during CPR [22]. It has previously been concluded that EtCO_2_ correlates well with blood flow and that PLR induces an increase in descending aortic blood flow of at least 10% or in echocardiographic sub-aortic flow of at least 12% [23-26]. In other studies, EtCO_2_ has been shown to be quantitatively predictive of stroke volumes [27]. EtCO_2_ has also been described as an important value for predicting ROSC and CPR quality [22,28,29]. The resuscitation in the Gothenburg pilot study was performed using both manual and mechanical compressions made by LUCAS TM 2 (Lund University Cardiac Assist System), but the effect of PLR appeared to be greater during manual compressions. It was only possible to speculate on the reason for this, but the EtCO_2_ value started from a higher level in the mechanical group. The possible reason for this could be the “active decompression” creating a larger preload.

Dragoumanos et al. [30] found in their animal study that the coronary perfusion pressure (CPP) also increased when PLR was performed during CPR and auto-transfusion of the aorta by PLR was the explanation. It is unclear whether this mechanism can be transferred to humans. The literature also includes some case reports and letters advocating PLR during CPR [31,32]. However, no studies showing that PLR during CPR will increase survival have been conducted.

### Hypothesis

The early elevation of the lower extremities during out-of-hospital cardiopulmonary resuscitation increases survival to one month by improving cardiac preload and blood flow to the heart and brain during chest compression.

## Design/method

### Population/area

Tarragona is a province in eastern Spain, in the southern part of the autonomous area known as Catalonia. The district of Tarragona has 814,000 inhabitants in an area of 6,303 km^2^. The population density is 128.2 inhabitants/km^2^ and 17.4% of the inhabitants live in the City of Tarragona and the surrounding areas. The rest are scattered throughout the province, which is composed of 183 municipalities distributed in ten areas. Coastal populations multiply their usual population by five during the months of July and August. The average age of the population is 40 years and 50.49% are men. There is a great deal of scatter in terms of the population throughout the area because of the large rural area that exists there.

### Organisation

Depending on the season, the Emergency Medical Service (EMS) system in Tarragona has around 70 units divided into eight advanced life support (ALS) units, including one helicopter, and 61 basic life support (BLS) units. The ALS units are staffed by one nurse, one physician and one technician and the BLS units by two technicians. Normally, the BLS units are the first responders in health emergencies, e.g. cardiac arrest. The Region of Tarragona has eight public hospitals, located around the region, with different levels of specialities and the highest levels are located in the City of Tarragona.

### Method and design

A prospective, randomized, controlled trial in which all patients (≥18 years) receiving out-of hospital CPR are randomized by envelope to be treated with either PLR or in a flat position. The ambulance crew use a special folding stool, which allows the legs to be elevated about 20 degrees.

The PLR manoeuvre needs to be performed immediately (within five minutes) after the arrival of the first ambulance. Leg elevation has to be maintained while the patient receives chest compressions during CPR and has to be stopped when the patient has an ROSC or when a medical decision is made to interrupt these maneuvers. PLR is to be performed at an angle of between 20 and 45 degrees (approximately 35 to 40 cm). An instruction video is produced for training prior to the study; the aim of using a specially designed folding stool is to standardise the intervention as much as possible.

In the start-up phase between June 2013 and April 2014, the study has only been conducted in the City of Tarragona and the surrounding areas. In all, 13 mobile units (12 BLS and one ALS unit) will attend (attended) in the start-up phase. Since April 2014, a further 56 units, the whole province, have been participating in the study. The study will continue for three years.

## Patient selection and randomization

### Inclusion/exclusion

#### Inclusion

All patients of both sexes who suffer an out-of-hospital cardiorespiratory arrest and require CPR and who are attended by the BLS and/or ALS units in the Tarragona area.

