#### Exclusion

Patients aged < 18 will be excluded from the study.

Allocation concealment is ensured via opaque, numbered and sealed envelopes. The random allocation lists are generated by a web-based automated randomization system. To guarantee a numeric balance across conditions the randomization will be performed separately in random permuted blocks of hundred. The allocation list will be kept in a remote secure location and an independent person randomly allocates the envelopes.

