### Study protocol, variables, part one (EMS)

Ambulance journal number, district, ambulance unit, date.

Randomization: yes (randomization number, PLR Y/N), no (forgot, <18 years, rigor mortis).

Time: of CA, call to dispatch centre, alert ambulance, start ambulance, arrival address, arrival at patient’s side, start CPR, first defibrillation, ROSC time, start transport to hospital, arrival hospital.

Patient data: age, gender, date of birth.

Data on the OHCA incident:

a) Place of occurrence (home, street…)

b) Witnessed: yes (bystander, ambulance staff), no

c) CPR before ambulance arrival: yes (layperson etc.…), no.

d) If CPR before ambulance: defibrillation Y/N (number), ventilation Y/N, chest compression Y/N, telephone CPR Y/N.

e) Status at ambulance arrival: unconscious Y/N, breathing (normal, agonal, no), pulse Y/N.

f) Initial rhythm:

g) Semi-automatic defibrillator: (defibrillation, no defibrillation).

h) If information about rhythm: (VF, VT, PEA, asystole).

i) Reason for CA: (cardiac cause, intoxication, drowning, suicide, accident, pulmonary disease, infant death, asphyxia, other reason).

j) Treatment: (chest compression, mechanical compression, ventilation, intubation, defibrillation (number), epinephrine, atropine, amiodarone, hypothermia.

k) Result: return of spontaneous circulation (ROSC), to hospital Y/N (if yes, which hospital).

l) If arrival hospital: pulse-giving rhythm Y/N, conscious Y/N.

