### Limitations

The power calculation is based on an estimated survival rate of 7%. If the survival rate is lower, we will need a larger sample than calculated. With regard to the outcome of the treatment during OHCA, it may be that the chance of survival does not increase. In no case, however, is there any risk to the participants.

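### The crew opens the envelope without checking that the legs can be raised, so patients who cannot receive PLR enter the comparison and may be coded out of the PLR arm only

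*Protocol article*

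**What the plan says.** All references are to the protocol article.

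- **Who is eligible.** The Inclusion section takes "All patients of both sexes who suffer an out-of-hospital cardiorespiratory arrest and require CPR and who are attended by the BLS and/or ALS units". The Exclusion section lists one criterion: "Patients aged < 18 will be excluded from the study". Method and design agrees: "all patients (≥18 years) receiving out-of hospital CPR are randomized by envelope to be treated with either PLR or in a flat position".
- **Order of events.** In the Clinical report form (CRF) section, one crew member confirms the arrest and starts compressions. The other opens the defibrillator bag, then the envelope, and uses the stool if PLR is drawn. No step before the envelope asks whether the legs can be raised.
- **Codes.** Study protocol, variables, part one (EMS) allows three reasons for not being randomised: forgot, age under 18, and rigor mortis. The CRF section also tells crews to mark forgot when PLR is done more than five minutes after CPR starts. For patients not included in the study, only the first part of the form is completed.
- **Aim and risk.** The Abstract asks whether early PLR also "has an impact on one-month survival in sudden and unexpected out-of-hospital cardiac arrest (OHCA". The Limitations section states: "In no case, however, is there any risk to the participants".

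**The concern.** The intervention acts through the legs, yet neither the criteria nor the crew's steps deal with a patient whose legs cannot be raised. If such a patient is drawn to the flat position, nothing unusual happens and the patient stays in the trial. If drawn to PLR, the intervention cannot be given and the crew must record something. The forgot code is the nearest option, and it classes the patient as not randomised although an envelope was opened.

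Two consequences follow. If these patients are recoded, they leave one arm only and the randomised comparison is no longer balanced for them. They may also go without follow-up, because 30-day death is recorded in part two of the form. If they are kept, as they should be once allocated, they add no treatment effect and shrink the difference that the trial is sized to detect.

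**Working it through.** **Inputs.** From Sample size, preliminary results and study period: 7% v 10% one-month survival, 80% power, two-sided 5%, 1,490 per arm. The share *f* of patients who cannot receive PLR is not given; 5% and 10% are assumptions. A 2% survival for these patients, used in one variant, is also an assumption.

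**The plan's own figure.** With p̄ = 0.085:

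n = [1.960√(2p̄(1−p̄)) + 0.842√(p₁(1−p₁)+p₂(1−p₂))]² / (p₂−p₁)²

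= (1.960×0.3944 + 0.842×0.3938)² / 0.03² = 1,356 per arm, or 1,422 with continuity correction.

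The stated 1,490 is larger than either. That is a separate matter; here it only supplies a margin.

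**Power at 1,490 per arm.**

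Power = Φ{[(p₂−p₁)√n − 1.960√(2p̄(1−p̄))] / √(p₁(1−p₁)+p₂(1−p₂))}

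Without dilution: (0.03×38.60 − 0.7730)/0.3938 = 0.978, so 83.6%. Exact enumeration for Fisher's test, which the plan names, gives 82.1%.

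**Kept in the trial, same 7% baseline.** PLR survival becomes 0.07 + 0.03(1−f).

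**Kept in the trial, assumed 2% survival in both arms.** Control is 0.07(1−f)+0.02f and PLR is 0.10(1−f)+0.02f. This gives 6.75% v 9.60% at 5%, and 6.50% v 9.20% at 10%.

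**Excluded before the envelope, not replaced.** n = 1,490(1−f), i.e. 1,415.5 or 1,341 per arm, at 7% v 10%.

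| f (assumed) | PLR survival, 7% baseline | Power, kept (7% baseline) | Power, kept (2% survival) | Power, excluded | Gain from exclusion, points |
|---|---|---|---|---|---|
| 0 | 10.00% | 83.6% | – | – | – |
| 5% | 9.85% | 80.0% | 81.1% | 81.7% | 0.6 to 1.7 |
| 10% | 9.70% | 76.0% | 78.3% | 79.6% | 1.3 to 3.6 |

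The margin before power drops below 80% is about 5% of patients without continuity correction (required n at f = 5% is exactly 1,490). With the correction it is just under 3% (required n at f = 3% is 1,502).

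**One-sided removal.** Suppose PLR does nothing, other patients survive at 7%, and those whose legs cannot be raised survive at the assumed 2%. If the latter are coded out of the PLR arm only, PLR shows 7.00% against 6.75% (f = 5%) or 6.50% (f = 10%). That is a false benefit of 0.25 or 0.50 points, or 8% or 17% of the planned 3-point difference. If they survive at the same 7%, this bias is zero; if they survive better, it reverses.

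**Wording side by side.** The aim speaks of sudden and unexpected arrest, while no criterion applies those words. The form has a rigor mortis code, while the Exclusion section does not list it. The no-risk sentence is absolute, while the article gives no reasoning that covers eligibility this broad.

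**The case against.** - **The population is deliberately broad.** Inclusion and Method and design describe all-comers, and so does the Hypothesis: "The early elevation of the lower extremities during out-of-hospital cardiopulmonary resuscitation increases survival to one month". A reader might infer that admitting arrests from accidents contradicts the aim. The documents do not support that: the aim is not limited to cardiac cause, and an arrest from an accident can be sudden and unexpected. The clearer gap is with expected arrests, such as terminal illness, which are also admitted.
- **The cause list proves little.** It reads "cardiac cause, intoxication, drowning, suicide, accident, pulmonary disease, infant death, asphyxia, other reason". One might take this as evidence that many accident victims will be randomised. It includes infant death in an adult trial, so it is a generic registry list, and part one is also completed for patients not included.
- **Dilution is assumed.** The documents give no share, and the 7% to 10% assumption is stated for out-of-hospital arrest generally. The described preload mechanism is not limited by cause of arrest, so only patients whose legs cannot be raised clearly gain nothing. They may be rare.
- **The forgot route is not certain.** The form also has a PLR yes/no field for randomised patients. A crew could use that, but the article does not say whether it records allocation or delivery.
- **Recruitment is tight.** About 300 patients a year are expected against 2 × 1,490 = 2,980, and a check during resuscitation is a burden.

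All of this stands. It removes the case for a blanket trauma exclusion and for calling the trial underpowered on this ground. It does not supply a feasibility check or a correct code.

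**Conclusion.** The point holds in a limited form, as a cheap improvement. Nothing identifies patients whose legs cannot be raised before allocation, and the nearest code for one drawn to PLR would wrongly class that patient as not randomised.

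On power, identifying them beforehand gains about 1 to 4 points, given an assumed share of 5% to 10% and an assumed survival of 2% or 7% in these patients. At 5% without continuity correction, power still meets the stated 80%. The protection against removal from one arm matters whatever the share, though the size of that bias depends on assumed survival.

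A reader might also infer that the no-risk sentence is contradicted by the enrolment of injured patients. The article reports no harm and mentions no such patients, so this is inference. What can be said is that the sentence is unqualified and the article gives no support for it across all eligible patients.

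**What to change.** 1. Add to the Exclusion section, and to step 1 of the CRF sequence, that patients in whom leg raising is not feasible are not randomised. The investigators define what counts. The criterion applies only while the envelope is sealed, so it cannot depend on allocation.
2. Add a matching reason for not being randomised to part one of the form, separate from forgot.
3. State that anyone whose envelope has been opened is followed up and analysed as allocated, whatever was delivered.
4. Reconcile the wording: the Abstract's aim with the all-adult criteria (rewording the aim is enough), the rigor mortis code with the Exclusion section, and the no-risk sentence in Limitations with the criteria. Whether traumatic arrests should be excluded is left to the investigators.

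**Cost.** One criterion, one CRF line, one form code and a few sentences. A few recruits are lost and crews make a brief judgement before opening the envelope. The trial has been running since June 2013, so the criterion applies prospectively; patients already randomised stay in the analysis as allocated.

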#### Exclusion

Patients aged < 18 will be excluded from the study.

Allocation concealment is ensured via opaque, numbered and sealed envelopes. The random allocation lists are generated by a web-based automated randomization system. To guarantee a numeric balance across conditions the randomization will be performed separately in random permuted blocks of hundred. The allocation list will be kept in a remote secure location and an independent person randomly allocates the envelopes.

**Figure 1 F1:**
[figure not shown]
CONSORT 2010 flow diagram.

### Outcome

Primary end-point: survival to one month.

Secondary end-point: survival to hospital admission to one month and to one year with acceptable cerebral performance classification (CPC) 1–2 [33].

Sub-group analysis: the result will also be analysed in relation to rhythm (shockable/non- shockable rhythm), age (more and less than 65 years), gender and ambulance delay (more and less than 10 minutes).

### Statistical methods

#### Descriptive statistics

The distribution of variables will be given as means, medians and percentages.

### Statistical analysis

Group comparisons (PLR/flat position) will be performed using Fisher’s non-parametric permutation test, the Mann–Whitney U test for continuous/ordered variables and Fisher’s exact test for dichotomous variables.

All tests will be two-tailed and p-values below 0.05 will be considered statistically significant.

### Data registration

The data registration will take place according to “Utstein style” [34] and will be linked to the existing web-based Swedish OHCA Registry. A two-step study protocol, translated into Spanish, is linked inside the Swedish OHCA Registry: part one is completed by the Spanish EMS staff and part two by the study co-ordinator, while part two will comprise follow-up patients admitted alive to hospital. The different parts have different security levels and log-ins. The data management and statistical analysis will be performed in Sweden by an independent statistician.

### Study protocol, variables, part one (EMS)

Ambulance journal number, district, ambulance unit, date.

Randomization: yes (randomization number, PLR Y/N), no (forgot, <18 years, rigor mortis).

Time: of CA, call to dispatch centre, alert ambulance, start ambulance, arrival address, arrival at patient’s side, start CPR, first defibrillation, ROSC time, start transport to hospital, arrival hospital.

Patient data: age, gender, date of birth.

Data on the OHCA incident:

a) Place of occurrence (home, street…)

b) Witnessed: yes (bystander, ambulance staff), no

c) CPR before ambulance arrival: yes (layperson etc.…), no.

d) If CPR before ambulance: defibrillation Y/N (number), ventilation Y/N, chest compression Y/N, telephone CPR Y/N.

e) Status at ambulance arrival: unconscious Y/N, breathing (normal, agonal, no), pulse Y/N.

f) Initial rhythm:

g) Semi-automatic defibrillator: (defibrillation, no defibrillation).

h) If information about rhythm: (VF, VT, PEA, asystole).

i) Reason for CA: (cardiac cause, intoxication, drowning, suicide, accident, pulmonary disease, infant death, asphyxia, other reason).

j) Treatment: (chest compression, mechanical compression, ventilation, intubation, defibrillation (number), epinephrine, atropine, amiodarone, hypothermia.

k) Result: return of spontaneous circulation (ROSC), to hospital Y/N (if yes, which hospital).

l) If arrival hospital: pulse-giving rhythm Y/N, conscious Y/N.

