### Clinical report form (CRF)

1. Staff member 1: confirm CA and start immediate chest compression.

2. Staff member 2: open defibrillator bag (with envelope and PLR reminder glued to the defibrillator).

3. Staff member 2: open envelope and randomize to PLR or flat position.

4. Staff member 2: if PLR, use the folding stool in the rescue bag.

5. Staff member 2: ventilate the patient once and attach defibrillation pads.

6. Continue resuscitation according to guidelines.

7. If PLR: keep the position as long as the patient is receiving chest compressions.

PLR has to be performed during the first minutes. If PLR is performed later than five minutes after the start of CPR: mark “forgot” on the data sheet.

Web registration: fill in the study protocol for all patients aged ≥18 years receiving out-of-hospital CPR. If not included in the study: just fill in the first part.

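### Rigor mortis is a non-randomisation reason on the data form but not an eligibility criterion, and nothing confines its use to the time before the envelope is opened

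*Protocol article*

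**What the plan says.** Three parts of the protocol article bear on who is in the trial.

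- **Eligibility.** Under *Inclusion*: "All patients of both sexes who suffer an out-of-hospital cardiorespiratory arrest and require CPR", if attended by the area's units. Under *Exclusion* there is one criterion: "Patients aged < 18 will be excluded from the study".
- **Data form.** *Study protocol, variables, part one (EMS)* has the field "Randomization: yes (randomization number, PLR Y/N), no (forgot, <18 years, rigor mortis". The randomisation number and the PLR indicator belong to *yes*; *no* carries a reason only.
- **Order of events.** In *Clinical report form (CRF)*, step 1 is "Staff member 1: confirm CA and start immediate chest compression", step 3 is "Staff member 2: open envelope and randomize to PLR or flat position", and step 4 is "Staff member 2: if PLR, use the folding stool in the rescue bag". Rigor mortis is not mentioned in these steps. The same section adds "If PLR is performed later than five minutes after the start of CPR: mark “forgot” on the data sheet" and, for patients left out, "If not included in the study: just fill in the first part".

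**The concern.** Take an adult with rigor mortis on whom CPR was started. The eligibility criteria admit this patient; the form allows the patient to be recorded as not randomised. The two texts define different trial populations, so the count of eligible patients in the flow diagram depends on which is used.

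The timing matters more. A reason for leaving a patient out is harmless if it is applied before anyone can know the arm. Here the crew opens the envelope at the patient's side and sees the allocation, and nothing stated closes the *no: rigor mortis* option at that moment. A patient removed for rigor is a certain non-survivor. If such removals differ between arms, the arm that loses more of them shows higher survival with no treatment effect, and the loss falls directly on the primary endpoint.

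**Working it through.** **Step 1: can the *no* field be filled in after opening?** The form gives three *no* reasons: forgot, under 18, rigor mortis. The CRF instruction on late PLR tells the crew to mark *forgot* when leg raising came more than five minutes after CPR began. A crew that raised the legs, late or not, has normally seen a PLR allocation. So at least one *no* reason is by instruction recorded after the arm is known. No text treats rigor mortis differently.

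**Step 2: would the form show the arm of a removed patient?** Not as described: number and PLR status sit under *yes* only, and a patient left out gets part one only. Part one does record whether the patient reached hospital, so for a patient truly in rigor what is lost is mainly the arm, not the outcome.

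**Step 3: the plan's own figure.** *Sample size, preliminary results and study period* gives 1,490 per arm for 7% against 10%, 80% power, two-sided 5%. The usual formula, with mean proportion 0.085, is

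n = [1.960·√(2·0.085·0.915) + 0.8416·√(0.07·0.93 + 0.10·0.90)]² / 0.03² = 1,356,

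or 1,422 with continuity correction. Neither gives 1,490; the stated number is somewhat generous (Fisher power 82.1%). That is a separate matter. I use 1,490 because it is the planned size.

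**Step 4: size of the bias.** Inputs: 7% survival in both arms (no true effect), 1,490 per arm, and Fisher's exact test at two-sided 5% (*Statistical analysis*). Assumption: a fraction f of the PLR arm, all deaths, is removed and none of the flat arm. The documents give no value for f. PLR survival becomes 0.07/(1−f), and the Fisher rejection rate is enumerated exactly.

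| f (assumed) | PLR patients left | PLR survival | Spurious gain (points) | False result favouring PLR |
|---|---|---|---|---|
| 0 | 1,490 | 7.00% | 0 | 2.1% |
| 1% | 1,475 | 7.07% | 0.07 | 2.8% |
| 2% | 1,460 | 7.14% | 0.14 | 3.4% |
| 5% | 1,416 | 7.37% | 0.37 | 5.4% |
| 10% | 1,341 | 7.78% | 0.78 | 11.5% |

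At 10% survival, the level the *Discussion* reports for Spain, the last column for f = 0, 1%, 2% and 5% is 2.2%, 2.9%, 3.5% and 6.4%. Mimicking the whole planned effect would need f = 1 − 0.07/0.10 = 30%.

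**The case against.** There is a good case that the form means something harmless. Rigor mortis stands under *Randomization: no*, which reads most naturally as a reason why no envelope was opened. The inclusion criterion asks that the patient require CPR, which can be taken to leave out a patient with rigor. The list is a log of non-randomised cases, not a list of exclusions, since *forgot* is no eligibility criterion. Envelopes are numbered and the allocation list is held remotely, so a used envelope could in principle be traced to its arm, and *Data collection* has the database compared with dispatch records. Finally, a journal article may leave the screening moment and the analysis population to the full protocol or SAP.

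Much of this stands, and it limits the point. It does not remove it. The benign reading is available but not fixed, and the *forgot* instruction cuts against it. Remote traceability helps only if someone links envelope numbers to patients recorded as *no*, which the form as described does not do. Nor is this only a matter of missing detail: the eligibility sections and the form differ on what they do state, and the article sets out the bedside order step by step.

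A reader might go further and infer that rigor is found only after the envelope is opened, and more often in the PLR arm because its legs are lifted, so that deaths leave that arm by design. The documents do not support this. Step 1, with the arrest confirmed and compressions begun, precedes the envelope, so rigor can be noticed there. Compressions, ventilation and pad placement involve close handling in both arms. No text says that rigor is recognised by lifting the legs.

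**Conclusion.** The point holds in a limited form. Eligibility and data form disagree on rigor mortis, and removal of a certain death after the allocation is seen is not prevented. That such removals occur, or occur more in one arm, is not shown. An excess in the PLR arm is plausible, because step 4 adds handling of the legs there, but it remains an inference.

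The size rests entirely on an assumed f. At 1–2% the distortion is small beside the 3-point target. At 5%, about 75 patients (0.05 × 1,490), the chance of a false finding for PLR is more than double its nominal level. The calculation assumes one-sided removal; equal removal in both arms would leave the comparison unbiased and change only the population. The defect merits correction because the remedy is cheap and protects the primary comparison in a trial whose crews know the allocation.

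**What to change.** 1. Make *Inclusion*, *Exclusion*, the part one form and the CRF steps agree on whether rigor mortis is an exclusion. The clinical decision is the sponsor's; the texts need to say the same thing.
2. If it stays as a reason for not randomising, accept *no: rigor mortis* on the form only when the envelope is still sealed, with a field that confirms this.
3. For every opened envelope, record *yes* with number and arm, complete follow-up, and analyse the patient in the allocated group. Rigor noticed after opening can be noted as a finding but does not change randomisation status.

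**Cost.** Some wording, one form rule and one data field; no change to treatment or sample size. The price is a few non-viable patients kept in both arms, which slightly dilutes any effect. If 2% of each arm were such patients and the planned 3-point gain held in the rest, the observable gain would be 0.98 × 3 = 2.94 points; at 5% it would be 0.95 × 3 = 2.85.
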